### Interventions

Study measures are captured in the schedule of assessments (Table 1). Study participants will attend study visits at weeks 0, 13, 26, 39, 52, 78, and 104. All participants will have MRI and X-ray scans within 4 weeks of biannual study visits from weeks 0 to 104. Clinical assessments, prognosis, and response to pharmacologic treatment will be assessed quarterly during the first year and biannually in the second. Study participants will be accrued over 1 year and followed for 2. At week 0 (baseline) and 104 weeks, all study participants will have an MRI conducted for the second to fifth MCPs of both hands. All participants will also have X-rays of both hands and feet conducted at baseline and 104 weeks.

**Table 1 T1:** Study schedule of assessments

**Assessment**	**Week**						
	**0**	**13**	**26**	**39**	**52**	**78**	**104**
Informed consent	X	X	X	X	X	X	X
OHIP number (each visit)	X	-	-	-	-	-	-
Demographics							
Date of birth	X	-	-	-	-	-	-
Gender	X	-	-	-	-	-	-
Race/ethnicity	X	-	-	-	-	-	-
Dominant hand	X	-	-	-	-	-	-
Household income (socioeconomic status)	X	-	-	-	-	-	-
Pack-years smoked	X	-	-	-	-	-	-
Medical history and comorbidities							
Surgeries	X	X	X	X	X	X	X
Conditions	X	X	X	X	X	X	X
Medications	X	X	X	X	X	X	X
Clinical assessment	X	X	X	X	X	X	X
Symptom duration	X	-	-	-	-	-	-
Morning stiffness duration	X	X	X	X	X	X	X
Swollen joint count	X	X	X	X	X	X	X
Tender joint count	X	X	X	X	X	X	X
Extra-articular features	X	X	X	X	X	X	X
Fatigue	X	X	X	X	X	X	X
Pain – Visual Analog Scale	X	X	X	X	X	X	X
Global physician impression of disease progression	X	X	X	X	X	X	X
Global patient impression of disease progression	X	X	X	X	X	X	X
Diagnostic imaging							
MRI – MCPs 2-5							
Worst-affected hand	-	-	X	-	X	X	-
Both hands	X	-	-	-	-	-	X
Radiography							
Both hands	X	-	X	-	X	X	X
Both wrists	X	-	X	-	X	X	X
Both feet	X	-	-	-	-	-	X
Laboratory tests							
Rheumatoid factor	X	O	O	O	O	O	O
Anti-citrullinated cyclic peptide antibodies level	X	-	-	-	-	-	-
Erythrocyte sedimentation rate	X	X	X	X	X	X	X
C-reactive protein	X	X	X	X	X	X	X
Other	X	X	X	X	X	X	X
Concomitant medications	X	X	X	X	X	X	X
Adverse events	X	X	X	X	X	X	X
Health-related quality of life							
Health assessment questionnaire	X	-	X	-	X	X	X
Health Utility Index Mark 3 and EQ-5D	X	-	X	-	X	X	X
Health resource utilization	X	-	X	-	X	X	X
Work and leisure time productivity	X	-	X	-	X	X	X

X, assessment conducted; O, assessment conducted only if preceding assessment negative.

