### Diagnostic image scoring

One of four radiologists will score each MRI and X-ray using the modified RAMRIS and vdHSS methods, respectively. Radiologists will be blinded to intervention allocation. The images sets will be anonymized and therefore scored independently from other acquisitions for the same patient. The modified RAMRIS or vdHSS adjusted for inter-rater reliability will be compared between the biannual diagnostic imaging time point and baseline, or to the time point when disease progression was last detected. For week 0 MRI, the modified RAMRIS of the worst-affected hand will be used as the reference score to determine changes. Total baseline tender and swollen joint count will determine the worst-affected hand. If joint counts are equal bilaterally, the participants’ self-reported dominant hand will be used to determine the reference score. For X-ray, the vdHSS for both hands and wrists will be compared biannually to monitor disease progression.

The inter-rater reliability across the four participating radiologists for scoring the RAMRIS and vdHSS, respectively, will be determined using baseline imaging data for the first nine study participants. A similar sample of images sets acquired from patients who first complete the 52-week study imaging requirements will be used to determine changes in SDD over time. The inter-rater SDD determined from the baseline sample will be used to determine adjusted modified RAMRIS and vdHSS scores at baseline and 26-week time points. The SDD determined at the 52-week time point will be used to adjust 52-, 78- and 104-week scores.

Changes in modified RAMRIS and vdHSS scores in magnitudes of SDD will be sent to the treating rheumatologist in the form of blinded diagnostic imaging reports for participants allocated to the MRI and X-ray treatment groups, respectively. For participants allocated to the sham-intervention group, negative reports will be sent. The SDD is a measure of the reliability specific to the raters and procedures of this study [58,59]:

(1)$$\mathrm{SDD}=1.96\times \sqrt{\frac{2\times \mathrm{SE}M_{\mathrm{STATUS}-\mathrm{SCORE}}}{k}}$$

OR

(2)$$\mathrm{SDD}=1.96*\frac{SD_{\mathrm{\Delta STATUS}-\mathrm{SCORE}}}{\sqrt{k}}$$

where *SEM*_*STATUS* − *SCORE*_ is the standard error of measurement of the status-score; *SD*_*ΔSTATUS* − *SCORE*_ is the standard deviation of the difference in status-score; *k* is the number of readings over which the analysis is averaged.

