Upon detection of an increase in RAMRIS or vdHSS of at least the SDD, a standardized blinded report will be sent to the rheumatologist indicating the status of disease progression for the patient, as follows:where < # > is the difference of the SDD-adjusted score between the two time points of interest rounded down to the whole number.

“Disease progression < # > -fold the smallest detectable difference was detected on < date of current MRI/X-ray > relative to < date of previous MRI/X-ray>. This disease progression consists of evolving synovitis, and/or edema, and/or joint space narrowing, and/or erosive damage.”

This calculation represents multifold differences in SDD. Disease progression reports sent to the rheumatologist will eliminate references to imaging modality, including reference to either RAMRIS or vdHSS, or of imaging features specific to either modality. These considerations will help maintain allocation concealment.

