### Standard of care

All study participants will receive the standard of care for disease management. They will attend clinical assessments quarterly for year 1 and biannually thereafter. Additional clinical visits are allowed per standard of care. The rationale for quarterly visits during the first year is two-fold: a period of sufficient duration to ensure slow-acting DMARDs take effect; a monitoring frequency conducive to detecting treatment adjustments over the early course of care for patients with newly-diagnosed RA or UIA. Pharmacotherapy will be monitored and adjusted over these clinical visits as per rheumatologist-dependent standard of care. Pharmacotherapeutic management of RA and UIA is modified based on monitoring a combination of clinical, laboratory, and diagnostic imaging assessments, in conjunction with patient therapeutic goals. Intra-articular or systemic corticosteroid therapy may be used per standard of care and will be documented. Generally, standard of care may vary by rheumatologist. As a result, the treating rheumatologist is included as a parameter in the minimization treatment allocation scheme.

Study rheumatologists will receive baseline MRI and X-ray reports for all study participants. Upon requisition of extra-study X-ray, the radiology report for the last study-derived images will be made available to the treating rheumatologist per standard of care, regardless of treatment allocation. In contrast, MRI is not standard of care for any of the study investigators and will not be provided. If no progression occurs between diagnostic imaging intervals, or if the participant is allocated to the standard of care intervention arm, negative diagnostic imaging reports will be reported to the treating physician.

As a historical control of standard of care, a chart audit of a randomly selected sample of study-eligible patients visiting the study rheumatologists 3 years preceding study enrolment will be conducted. The chart audit will be used to determine the frequency of diagnostic imaging requisition and treatment escalation. Rates of diagnostic imaging and treatment escalation between the study and historical control will provide a measure of standard of care bias in the study [60] - that is, to determine if either diagnostic imaging or treatment escalation occur more or less frequently within the study than in clinical practice for the same setting.

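### The progression report prints the scan dates, which can disclose MRI versus X-ray when the two scans fall on different days and the rheumatologist can link a date to a scan

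*Protocol article*

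**What the plan says.** The Diagnostic image scoring section of the Protocol article states the aim of the report: "Disease progression reports sent to the rheumatologist will eliminate references to imaging modality, including reference to either RAMRIS or vdHSS". It adds: "These considerations will help maintain allocation concealment". The template in the same section nevertheless says that progression "was detected on < date of current MRI/X-ray > relative to < date of previous MRI/X-ray>".

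Four other statements bear on what those dates give away:

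- **Which score is reported** (Diagnostic image scoring): changes in the MRI and X-ray scores are sent "for participants allocated to the MRI and X-ray treatment groups, respectively". Sham participants always get a negative report.
- **Reference scan** (Diagnostic image scoring): scores "will be compared between the biannual diagnostic imaging time point and baseline, or to the time point when disease progression was last detected".
- **Scan timing** (Interventions): "All participants will have MRI and X-ray scans within 4 weeks of biannual study visits from weeks 0 to 104".
- **What the rheumatologist holds** (Standard of care): "Study rheumatologists will receive baseline MRI and X-ray reports for all study participants". A request for an extra-study X-ray also releases the radiology report of the latest study X-ray. Follow-up MRI reports are not released.

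The Study design section describes concealment as withholding images and imaging features at follow-up. It does not mention dates.

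**The concern.** The report strips out the scoring system and the features specific to each modality, but leaves in a date that belongs to only one of the two scans. Every participant has both scans at each imaging time point. When they are on different days, the printed date matches one and not the other, and anyone who knows the two dates can read off the modality.

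The person who would be unblinded is the person who generates the outcome. The Primary outcome section defines the endpoint as any change of DMARD agent or any dose escalation, which is the treating rheumatologist's decision. The Standard of care section says MRI is not routine for any of these physicians, and the Discussion raises false-positive MRI erosions. It is plausible that a result known to come from MRI would be weighed differently from one known to come from X-ray. The MRI versus X-ray contrast would then mix the information in the image with the physician's opinion of the modality, which the blinded report is designed to prevent.

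**Working it through.** The protocol gives no figure for this risk, so the check is mainly a comparison of passages.

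**1. Is the printed date specific to one modality?** The template has one placeholder for the current scan and one for the reference scan. Only the allocated modality's score is reported. One date per time point is therefore most naturally that modality's scan date. No passage substitutes a visit date or a common imaging date.

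**2. Can the two scans be on different days?** Yes. The Interventions section gives a window of 4 weeks around the visit and no same-day rule. The scans could be up to 4 weeks apart if the window lies on one side of the visit, and up to 4 + 4 = 8 weeks if it runs both ways. The text does not say which.

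**3. Can the rheumatologist link a date to a scan?** There are three routes with some basis in the document:

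- *Baseline reports.* The reference is baseline until progression is first detected, so a participant's first positive report cites the baseline scan date. The rheumatologist has both baseline reports. If they carry dates (an assumption) and the baseline scans were on different days, the match is immediate.
- *Study X-ray report on requisition.* This could give the follow-up X-ray date, but only when an extra-study X-ray is requested.
- *The patient*, who attended both scans and may recall the days.

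**4. What does the date add to a positive report?** Sham participants never receive a positive report, and the Study design section says the rheumatologists are informed of the protocol. A positive report, dated or not, already shows that the participant is in an active arm. The date can add only MRI versus X-ray.

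**5. Ceiling on the number affected.** Inputs from the Sample size section: 36% progression for MRI, 25% for X-ray, 62 participants per group.

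- MRI arm: 0.36 × 62 = 22.3
- X-ray arm: 0.25 × 62 = 15.5
- Total: 22.3 + 15.5 = 37.8, about 38 of 2 × 62 = 124 active-arm participants

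With the approximately 45 per group before inflation for remission, attrition and missing data, the total is (0.36 + 0.25) × 45 = 27.5, about 27. Either figure counts participants with a positive report, not participants whose modality is disclosed.

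**6. Why the ceiling cannot be narrowed.** Let q be the share of time points at which both scans are on the same day, and treat time points as independent. Each report prints two dates, so at least one is specific to a modality with probability 1 − q²:

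| q (assumed) | 1 − q² |
|---|---|
| 0 | 100% |
| 0.5 | 75% |
| 0.75 | 44% |
| 0.9 | 19% |
| 1 | 0% |

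The document does not give q, so the whole range is open. Even these percentages overstate disclosure, because they assume that every differing date is recognised.

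**The case against.** The best defence is that disclosure depends on two facts the document does not state: scans on different days, and a rheumatologist who knows which was when. If both scans are done at one attendance, nothing leaks. The placeholder could be filled with one common imaging date, and booking and form-completion rules are commonly left to a full protocol or study manual. The section also claims only that its measures help to maintain concealment, not that they guarantee it. All this stands and limits the point to a possible leak. It does not remove it: the article prints the template itself, and the natural reading of that template works against the aim stated beside it.

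Three stronger readings are tempting and are not supported:

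- *Different scan days always reveal the modality.* They do not, because someone must also link the date to the scan. Follow-up MRI reports are withheld, and the study X-ray report is released only on requisition.
- *The date tells the rheumatologist that the patient is not in the sham group, so that later negative reports are genuine.* The positive result itself shows this, and removing the date would leave it unchanged. The comparisons with sham could be touched only indirectly, if reacting differently by modality shifted an active arm's escalation rate.
- *A definite number of participants will be unblinded.* Any such number needs an assumed share of different-day scans and an assumed rate of recognition, and neither has an anchor in the document.

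**Conclusion.** The point holds in conditional form. On its natural reading, the template prints the allocated modality's scan dates in a report meant to remove every trace of modality, and nothing in the article closes that gap. A positive report can therefore disclose MRI versus X-ray if the scan days differ and the rheumatologist can link a date to a scan. The baseline route is the clearest, provided those reports are dated.

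The likely harm is to the MRI versus X-ray comparison of the primary endpoint. Its direction cannot be stated. Its frequency cannot be computed: at the planning rates about 38 of 124 active-arm participants is an upper bound, and the true number could be zero if scans are always done on the same day. Confidence is moderate. The change is worth making because it costs almost nothing and protects an endpoint that is the blinded physician's own decision.

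**What to change.** Replace both scan dates in the template with the study visit label, for example *week-52 study imaging relative to week-0 study imaging*, or with one common visit date for both modalities. Use the same format in every report, including negative and sham reports. The wording of negative reports is not shown, so including them is a precaution for uniformity.

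This is a wording change that alters no scan, score or clinical rule. The rheumatologist loses the exact scan day. The Trial status section describes the trial as ongoing, so any dated reports already sent cannot be changed, and the trial would then contain two report formats. The date of the switch should be recorded.

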### Standard of care

All study participants will receive the standard of care for disease management. They will attend clinical assessments quarterly for year 1 and biannually thereafter. Additional clinical visits are allowed per standard of care. The rationale for quarterly visits during the first year is two-fold: a period of sufficient duration to ensure slow-acting DMARDs take effect; a monitoring frequency conducive to detecting treatment adjustments over the early course of care for patients with newly-diagnosed RA or UIA. Pharmacotherapy will be monitored and adjusted over these clinical visits as per rheumatologist-dependent standard of care. Pharmacotherapeutic management of RA and UIA is modified based on monitoring a combination of clinical, laboratory, and diagnostic imaging assessments, in conjunction with patient therapeutic goals. Intra-articular or systemic corticosteroid therapy may be used per standard of care and will be documented. Generally, standard of care may vary by rheumatologist. As a result, the treating rheumatologist is included as a parameter in the minimization treatment allocation scheme.

Study rheumatologists will receive baseline MRI and X-ray reports for all study participants. Upon requisition of extra-study X-ray, the radiology report for the last study-derived images will be made available to the treating rheumatologist per standard of care, regardless of treatment allocation. In contrast, MRI is not standard of care for any of the study investigators and will not be provided. If no progression occurs between diagnostic imaging intervals, or if the participant is allocated to the standard of care intervention arm, negative diagnostic imaging reports will be reported to the treating physician.

As a historical control of standard of care, a chart audit of a randomly selected sample of study-eligible patients visiting the study rheumatologists 3 years preceding study enrolment will be conducted. The chart audit will be used to determine the frequency of diagnostic imaging requisition and treatment escalation. Rates of diagnostic imaging and treatment escalation between the study and historical control will provide a measure of standard of care bias in the study [60] - that is, to determine if either diagnostic imaging or treatment escalation occur more or less frequently within the study than in clinical practice for the same setting.

### Outcomes

#### Primary outcome

The primary outcome of the study is DMARD treatment augmentation over 2 years. All changes in DMARDs and/or biologic treatment over the course of the study will be recorded. The primary endpoint definition is any change in DMARD agent or dose escalation. A co-primary endpoint is diagnostic imaging evidence of disease progression. Clinical radiology reports of the disease progression from discretionary diagnostic imaging requisitions will count towards the assessment of the co-primary endpoint.

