**Methods:**

A double-blind, randomized controlled trial has been designed. Rheumatoid and undifferentiated inflammatory arthritis patients will undergo an MRI and X-ray assessment every 6 months. Baseline adaptive randomization will be used to allocate participants to MRI, X-ray, or sham-intervention groups on a background of standard of care. Prognostic markers, treating physician, and baseline DMARD therapy will be used as intervention allocation parameters. The outcome measures in rheumatology RA MRI score and the van der Heijde-modified Sharp score will be used to evaluate the MRI and X-ray images, respectively. Radiologists will score anonymized images for all patients regardless of intervention allocation. Disease progression will be determined based on the study-specific, inter-rater smallest detectable difference. Allocation-dependent, intervention-concealed reports of positive or negative disease progression will be reported to the treating rheumatologist. Negative reports will be delivered for the sham-intervention group. Study-based radiology clinical reports will be provided to the treating rheumatologists for extra-study X-ray requisitions to limit patient radiation exposure as part of diagnostic imaging standard of care. DMARD treatment dose escalation and therapy changes will be measured to evaluate the primary objective. A sample size of 186 (62 per group) patients will be required to determine a 36% difference in pharmacological treatment escalation between the three groups with intermediate dispersion of data with 90% power at a 5% level of significance.

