## Methods/design

### Study design

The study is a three-group, double-blind, randomized controlled trial (Figure 1). The interventions include 1.0 T extremity MRI of the second to fifth MCPs of the worst-affected hand (determined by cumulative swollen and tender joint count at baseline) and X-ray of both hands using lateral, anteroposterior, and oblique views. The two interventions will be superimposed on standard of care. All groups, including the sham-intervention group, will receive standard of care diagnostic imaging feedback. Participants will be assigned to one of the three interventions using minimization, also known as baseline adaptive randomization [41,42]. The prognostic factors for intervention allocation were determined from recent American College of Rheumatology anti-rheumatic treatment recommendations [43]. Intervention allocation will be concealed by having all study participants undertake both diagnostic imaging scans at all time points: one-third will have positive or negative reports of disease progression reported back to the rheumatologist based on MRI scores; one-third will have X-ray-based results reported; and one-third will always have negative reports returned to the rheumatologist. Study rheumatologists are informed of the study protocol. They are aware that one-third of the negative results will not be based on imaging findings and are allowed to prescribe X-ray diagnostic imaging as part of standard of care. All image sets will be anonymized per assessment and scored independently by one of four radiologists using the van der Heijde-modified Sharp Score (vdHSS) for X-ray [44-46] and a non-contrast modification [47] of the OMERACT RAMRIS for MRI [24]. At the beginning of the study, and mid-way through follow-up, a sample of nine image sets for each modality will be read by all four radiologists to determine the inter-rater smallest detectable difference (SDD).

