**Figure 1 F1:**
[figure not shown]
**Study participant flow diagram and intervention allocation prognostic variables.** Anti-CCP, anti-citrullinated cyclic peptide antibodies; BRM, biologic response modifier; DMARD, disease-modifying anti-rheumatic drug; DAS28, 28-joint disease activity score; MCP, metacarpophalangeal joint; MRI, magnetic resonance imaging.

The SDD in imaging scores will be used to adjust for inter-rater reliability in the diagnostic imaging scores. Differences in SDD-adjusted scores will be used to determine disease progression. The analyst determining the SDD will be blinded to patient intervention allocation. Intervention allocation will be concealed from treating rheumatologists by reporting disease progression as changes in SDD magnitudes with follow-up disclosure of neither images, nor imaging features. The selection of the anatomy to compare and the frequency of intervention was based on the following considerations: anatomy most commonly scanned over follow-up in this population [40], least anatomy required to visualize greatest change in disease progression [14,15], and minimization of both radiation exposure for X-ray and MRI scan time.

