### Statistical analysis

#### Sample size

A sample size of 186 RA and UIA patients was estimated from a one-way analysis of variance statistical test to determine a difference in the rate of pharmacological treatment escalation between imaging interventions over 2 years between three groups with intermediate dispersion of data [74].

(3)$$f=\frac{d}{2}\sqrt{\frac{\left(k+1\right)}{3\left(k-1\right)}}$$

where *f* is the analysis of variance effect size; *k* is the number of groups being compared; and *d* is the standardized effect size,

(4)$$d=\frac{\delta }{s}$$

where, *δ* is the difference between the greatest and least group mean; and *s* is the standard deviation.

This parametric test is sufficiently robust to yield sample size estimates for non-parametric data [74].

Treatment escalation was assumed to be directly proportional to disease progression. The rate of X-ray progression over 2 years [75] was taken together with 1-year MRI and X-ray progression data [15] to estimate testing between 36% MRI progression of the second to fifth MCPs joints of a single hand, 25% radiographic progression of bilateral hands and wrists, and no progression for the standard of care group. Although some patients may progress several-fold over the clinically relevant threshold, progression was conservatively assumed to result in a single pharmacological treatment escalation per affected participant, since a change in therapy is expected to introduce an incremental protective effect.

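### Counting clinical reports from discretionary X-ray requisitions towards the co-primary imaging endpoint could let ascertainment differ by arm

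*Protocol article*

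**What the plan says.** Under Primary outcome the article states: "A co-primary endpoint is diagnostic imaging evidence of disease progression". It then adds: "Clinical radiology reports of the disease progression from discretionary diagnostic imaging requisitions will count towards the assessment of the co-primary endpoint".

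Elsewhere it sets up ascertainment that does not depend on the arm:

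- Study design conceals allocation by "having all study participants undertake both diagnostic imaging scans at all time points".
- The same section says of the readings: "All image sets will be anonymized per assessment and scored independently by one of four radiologists". The abstract confirms this: "Radiologists will score anonymized images for all patients regardless of intervention allocation".
- The text after Figure 1 gives the threshold: "Differences in SDD-adjusted scores will be used to determine disease progression".

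The discretionary route is described under Standard of care. When a rheumatologist requests an X-ray outside the study schedule, "the radiology report for the last study-derived images will be made available to the treating rheumatologist per standard of care, regardless of treatment allocation". MRI reports are not released this way. The abstract gives the purpose as limiting radiation exposure.

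Study design also says what the rheumatologists know. They receive progression reports that depend on allocation (always negative in sham), they know that some negative reports are not based on images, and they may order X-rays.

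**The concern.** The scheduled readings treat the three arms alike in timing, modality, reader blinding and threshold. The discretionary reports differ on three counts:

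- **Trigger.** The treating rheumatologist decides whether to requisition, after feedback whose content differs by arm. Blinding to allocation does not close this path, because the content of the report is itself the intervention.
- **Threshold.** The article ties a clinical report of progression to no SDD. Study scoring keeps a participant's images from being compared over time (Blinding), so a statement of progression in a clinical report must come from a different reading process.
- **Modality.** Only X-ray is available by this route.

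A requisition thus gives a selected participant a second chance to be called progressed. If requisitions among otherwise event-free participants differ by arm, the co-primary comparison partly measures ordering behaviour. More requisitions in the imaging arms would make those arms look worse. More in sham would make imaging-guided care look better.

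**Working it through.** **Plan's own figure.** The article gives no rate, effect size or sample size for the co-primary endpoint. Its 62 per group was derived for treatment escalation: 45 / (0.95 × 0.85 × 0.95²) = 61.7, using the stated allowances for remission, missing data and two years of attrition. It is used below only as the group size.

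**Inputs, all assumed.** The article states none of these for this endpoint.
- p = proportion progressing by SDD on scheduled scores, equal in all arms: 0.25
- r = proportion with a discretionary requisition among participants not already counted: a gap between arms of 0.20 to 0.40
- q = chance that a clinical report calls progression when the SDD score does not: 0.10 to 0.30

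**Formula.** Recorded progression in an arm = p + (1 − p) × r × q. With p and q equal across arms, the spurious difference is (1 − p) × (gap in r) × q.

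**Results at p = 0.25.**
- Gap 0.20: 0.75 × 0.20 × 0.10 = 1.5 points; with q = 0.30, 0.75 × 0.20 × 0.30 = 4.5 points.
- Gap 0.40: 0.75 × 0.40 × 0.10 = 3.0 points; with q = 0.30, 0.75 × 0.40 × 0.30 = 9.0 points.
- Gap 0: no spurious difference, whatever q is.

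Reversing which arm has more requisitions reverses the sign.

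**Effect on the test.** As a proxy for the planned Cochran-Mantel-Haenszel test, take a three-group chi-square (2 df, 62 per arm), with requisitions in 50% of both imaging arms and 20% of sham. At q = 0.30 the recorded rates are 0.25 + 0.75 × 0.50 × 0.30 = 0.3625 (imaging arms) and 0.25 + 0.75 × 0.20 × 0.30 = 0.295 (sham), with mean 0.34. The noncentrality is 62 × (2 × 0.0225² + 0.045²) / (0.34 × 0.66) = 0.84, and the type I error is 11.9% instead of 5%. At q = 0.10 and 0.20 the difference is 2.25 and 4.5 points, and the type I error 5.8% and 8.1%.

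**After the fix.** With scheduled SDD-based scores only, r and q drop out. The expected difference under equal progression is 0 and the error rate is the nominal 5%.

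**The case against.** **The rule may be deliberate.** The co-primary objective compares imaging evidence of progression under each monitoring strategy, and standard-of-care imaging continues in all arms. On that view, discretionary imaging is how the comparator arm detects progression. This does not rescue the rule. The article defines progression by SDD-adjusted scores and hopes that monitoring will hinder it, which makes it a disease outcome. The sham arm is scanned and scored like the others, so it needs no separate route.

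**Release of the report does not depend on allocation.** True, but that governs access once a requisition is made, not how often one is made. The planned chart audit compares the study with past practice, not arm with arm.

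**Many participants with a positive report already count as progressed.** This stands in part. The gap that matters is among participants not already counted. In the X-ray arm, for example, someone below the SDD on X-ray gets a negative report, just as in sham. The path needs cases such as a positive MRI report with an X-ray score below the SDD, if the X-ray score defines the endpoint, or a positive report at a visit other than the one analysed. The relevant gap may therefore be smaller than the gap in overall requisitions.

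**Stronger readings that a reader might infer.** The text does not support these:
- That ascertainment does depend on the arm. Without requisition rates, only *could* is justified.
- That more requisitions mean more films. A requisition generally releases a report on study films already scored, so the extra chance is a second reading.
- That the arms will be compared on different instruments, because Sample size assumes MRI progression in one arm and "25% radiographic progression of bilateral hands and wrists, and no progression for the standard of care group". Those rates were chosen to size the escalation endpoint, and both modalities are scored in every arm. For the same reason, the 11-point gap between 36% and 25% is no planned contrast for this endpoint and no yardstick for the bias.

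**Conclusion.** The point holds as a risk built into the endpoint rule. The article affirmatively counts a source that is requested selectively, covers one modality and has no SDD threshold, although a complete scheduled and blinded source exists. It describes no adjudication or restriction that would neutralise this. The possible bias is 1.5 to 9 points on the assumptions shown, and zero if requisitions among otherwise event-free participants are equal across arms. Neither the size nor the direction can be known from the document. The scheduled part of the endpoint and the sample size for treatment escalation are not affected.

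**What to change.** Remove discretionary clinical reports from the co-primary endpoint. Define it as an increase of at least one SDD on the scheduled, anonymised, blinded scores, by the same rule in all three arms. Report the number of discretionary requisitions and their findings by arm as descriptive data, or add them only in a sensitivity analysis.

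The cost is small but not nil. The trial is ongoing, so the endpoint wording needs an amendment, best made before the blind is broken. A few events seen only on clinical reports would no longer count. No further images, visits or participants are needed, because all scheduled images are already planned to be scored in every arm.
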